#### **Data Analyses:**

The analytic approach is built upon the investigative team's prior HIV prevention randomized clinical trials. An intention-to-treat approach will be used. To enhance the rigor of an intention-to-treat analytic approach, we will employ multiple imputation to handle missing data, attrition analyses to investigate non-ignorable nonresponse, and sensitivity analyses to ascertain robustness of findings against violation of model assumptions (e.g., distribution requirements, heteroscedasticity, independence). Multiple imputation will be implemented using the imputation by chained equations algorithm (ice) in the statistical software Stata. This procedure allows specifying linear regression to impute continuous variables, logistic regression to impute dichotomous variables, multinomial logistic regression to impute categorical variables, and negative binomial regression to impute count data. Specifications of the imputation model will be based on the information that is observed or measured for a participant at prior assessments to predict values for variables that are missing, including covariates from the baseline assessment and behavioral outcome variables at the baseline and each follow-up assessment. The analysis plan is also informed by earlier RCTs of couple-based interventions. Generalized Linear Mixed Models (GLMM) will be used to account for the non-independence in measures arising from: (1) "autocorrelation" due to repeated measures with the same person; and (2) "intraclass correlation [ICC]" arising from partners who are reporting on conjoint behaviors. These models build upon  $g(E[(Y_{ij} | \mathbf{x}_{ij})]) = \mathbf{x}'_{ij} \boldsymbol{\beta}$  where  $Y_{ij}$  is the outcome variable of interest for the  $i$ th participant at the  $j$ th timepoint. The multilevel nature of the data are accounted for by modeling each predictor variable's coefficient in the vector  $\boldsymbol{\beta}$  as dependent on couple membership:  $\beta_i = \mathbf{w}_g \boldsymbol{\gamma}$  where the  $i$ th participant is part of the  $g$ th couple which determines the couple characteristics (i.e., elements of the vector  $\mathbf{w}$ ) used to estimate model fit parameters in vector  $\boldsymbol{\gamma}$ . The components of  $\boldsymbol{\beta}$  will be

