treatment assignment, baseline attributes for the outcome variable, and those variables selected during preliminary analyses as noted earlier. The  $g(a)$  function represents a link function that can properly model the outcome variable as a function of measurement unit or distribution. Hypothesis testing follows the form “Assignment to PACT will be associated with significantly lower/higher on outcome variable Y at the 12-month follow-up compared to assignment to HIV CTR” where ‘lower’ or ‘higher’ is chosen in the direction of reduced risk. Outcome-specific modeling information for hypothesis testing is presented in Table 1.

| Table 1: Data Analytic Approach for Hypotheses Testing                                                                                                                                                                       |                                                        |                                                                   |                                                                                                      |
|------------------------------------------------------------------------------------------------------------------------------------------------------------------------------------------------------------------------------|--------------------------------------------------------|-------------------------------------------------------------------|------------------------------------------------------------------------------------------------------|
|                                                                                                                                                                                                                              | Y                                                      | Candidate* link function
g(a)                                  | Covariates used to
estimate $\beta$ & $\gamma$                                                    |
| H 1                                                                                                                                                                                                               | • Incidence of Chlamydia,
trichomonas and gonorrhea | • Logistic:
$\log(a/(1 - a))$
• Poisson: $\log(a)$          | • Baseline
attributes for
sociodemographics

• Attribute(s) of Y
measured at baseline |

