| H 2                                                                                                                                                                                                               | • # of acts of unprotected
intercourse              | • Poisson: $\log(a)$
• Negative Binomial:
$\log(a/(k + a))$ |                                                                                                      |
| H 3                                                                                                                                                                                                               | • # of sexual partners                                 | • Poisson: $\log(a)$
• Negative Binomial:
$\log(a/(k + a))$ |                                                                                                      |
| H 4                                                                                                                                                                                                               | • # of days in which no illicit
drugs were used     | • Poisson: $\log(a)$
• Negative Binomial:
$\log(a/(k + a))$ |                                                                                                      |
| H 5                                                                                                                                                                                                               | • Drug Treatment
Attendance/Engagement              | • Logistic:
$\log(a/(1 - a))$                                  |                                                                                                      |
| Candidate link functions (beyond distributional requirements) will be determined by selecting the function with the best overall fit metrics followed by statistical efficiency of the coefficient for study arm assignment. |                                                        |                                                                   |                                                                                                      |

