**Power Analysis:** Power analyses were conducted using G\*Power (v3.1.0). Autocorrelation ( $\rho$ ) and ICC estimates were based on Project PACT trial and Pilot of Revised PACT in CCP settings. From ICC estimates, variance inflation factors were calculated to generate effective sample sizes. Outcome estimates for intervention effects were obtained from Project PACT while those for HIV CTR used PACT wellness promotion comparison condition as a proxy for non-specific attention. These estimates allow for effect size  $f^2$  to be calculated. For cumulative STI incidence, we assumed a 50% reduction to be clinically meaningful to detect via Poisson regression. Results for primary outcomes indicate that a minimum of 80% power is achieved for all primary outcomes with 96 couples per arm. Based on the team’s successful retention in Project WORTH with drug-involved offenders and prior couple-based studies for the likelihood of 80% to 85% retention, this is corresponding to 113 to 120 couples per arm (or a total of 226 to 240 couples) before 15% to 20% attrition. Power analyses with 96 participants per arm indicate 80% power to detect differences for effect sizes  $f^2 = .03$  to  $.04$  (for  $\rho = .1$  TO  $.5$ ), indicating the ability to detect substantially smaller than “medium” effect sizes (Cohen, 1988).

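### Table 1 gives the negative binomial candidate for H2–H4 the link log(a/(k + a)) instead of log(a), so its arm coefficient is not a log rate ratio and fits badly with the planned mixed model

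*Protocol*

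**What the plan says.** The Data Analyses section of the protocol sets a generalized linear mixed model in which g is applied to the conditional mean of the outcome, "where $Y_{ij}$ is the outcome variable of interest for the $i$ th participant at the $j$ th timepoint". It then says that the g(a) "function represents a link function that can properly model the outcome variable as a function of measurement unit or distribution". So a is the mean, and the column of Table 1 holding g(a) is a list of links, not of variances or densities.

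For H2 (acts of unprotected intercourse), H3 (sexual partners) and H4 (days without illicit drugs), that column has two entries: Poisson with log(a), and "Negative Binomial: $\log(a/(k + a", in full log(a/(k + a)). The protocol does not define k.

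The note under the table settles the choice by "selecting the function with the best overall fit metrics followed by statistical efficiency of the coefficient for study arm assignment". The hypotheses are directional: "Assignment to PACT will be associated with significantly lower/higher on outcome variable Y at the 12-month follow-up compared to assignment to HIV CTR". No rate ratio or other effect measure is named for H2–H4.

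**The concern.** Count regression with a negative binomial variance is normally run with a log link, so that the exponentiated arm coefficient is a ratio of means. The link in Table 1 does something else, with three consequences if that candidate is chosen.

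- The size of the arm coefficient depends on the dispersion parameter and on the level of the mean, so it has no direct reading as a proportional reduction in risk behaviour.
- log(a/(k + a)) is below zero for every positive a and k, so the linear predictor has a ceiling. The planned mixed model adds couple-level and person-level variation to that predictor.
- Poisson and negative binomial would differ in effect scale as well as in variance. The selection rule in the table note then compares coefficients that do not measure the same thing.

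At stake are the interpretation of the effect, the choice between models and the stability of the fit.

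**Working it through.** **The plan's own figure.** The only sample-size arithmetic on hand is the attrition adjustment. The Power Analysis says that "a minimum of 80% power is achieved for all primary outcomes with 96 couples per arm" and that "this is corresponding to 113 to 120 couples per arm (or a total of 226 to 240 couples) before 15% to 20% attrition". 96/0.85 = 113 and 96/0.80 = 120, so it reproduces. Nothing in it depends on the link at issue.

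**Inputs.** From the protocol: g acts on the mean, and the two candidate links. Assumed, because the protocol gives neither: the control mean a0 and the dispersion k. I read k as the negative binomial size parameter, with variance a + a²/k.

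**Arm coefficient.** Let a1 be the PACT mean and RR = a1/a0. Then

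beta = log[a1/(k + a1)] − log[a0/(k + a0)], so exp(beta) = RR × (k + a0)/(k + a1).

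This equals RR only when RR = 1 or as k goes to infinity. For a true RR of 0.50 with a0 = 10 and a1 = 5:

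| k | exp(beta), listed link | exp(beta), log link |
|---|---|---|
| 0.5 | 0.5 × 10.5/5.5 = 0.955 | 0.50 |
| 1 | 0.5 × 11/6 = 0.917 | 0.50 |
| 2 | 0.5 × 12/7 = 0.857 | 0.50 |
| 5 | 0.5 × 15/10 = 0.750 | 0.50 |
| 50 | 0.5 × 60/55 = 0.545 | 0.50 |

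With k held at 1, the same halving reads 0.750 at a0 = 2, 0.917 at a0 = 10 and 0.969 at a0 = 30.

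**The reverse direction.** Take one fitted value, exp(beta) = 0.90, with k = 1. Put q = 0.90 × a0/(1 + a0) and a1 = q/(1 − q). At a0 = 10, q = 0.818 and a1 = 4.5, so RR = 0.45. The same coefficient means RR = 0.75 at a0 = 2 and 0.225 at a0 = 30. Since Table 1 adjusts for baseline attributes, a single coefficient would imply a different ratio of means at each covariate level.

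**The ceiling.** At a0 = 10 and k = 1 the linear predictor is log(10/11) = −0.095. A couple whose random deviation exceeds +0.095 has no valid mean. For H4, where benefit is an increase, assume a0 = 60 and k = 1: exp(beta) cannot exceed 61/60 = 1.017, and a true 30% increase shows as 1.3 × 61/79 = 1.004.

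**The selection rule.** The derivative of log(a) is 1/a; that of log(a/(k + a)) is k/[a(k + a)]. For the same data and variance, the delta-method standard error under the listed link is smaller by the factor k/(k + a), which is 1/11 at a = 10 and k = 1. If efficiency is read as a smaller standard error, the listed link gains from its scale alone.

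**The test of no difference.** beta = 0 if and only if a1 = a0. In a simulation of 4,000 runs (192 per arm, a0 = 10, k = 1 treated as known, no clustering or covariates), Wald tests gave:

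| | Log link | Listed link |
|---|---|---|
| Size, RR = 1 | 0.049 | 0.046 |
| Power, RR = 0.7 | 0.917 | 0.914 |

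**The case against.** The strongest reply is that the entry is a legitimate function. It is the canonical link, the logit and log entries are canonical too, and the list may have been drawn up that way. It is only one of two candidates. The protocol promises no rate ratio, only a direction, and the effect measure to be reported may be left to an analysis plan that is not shown. All of this stands. The point is therefore a badly fixed scale, not an algebraic error or an internal contradiction.

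It can also be said that software usually defaults to the log link, so the table may never be followed literally. That lowers the practical risk but is a reason to correct the table. The boundary problem with random effects follows from the algebra; no mixed model was fitted to see how often it would bite.

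A third reply is that the H1 row pairs logistic with Poisson log, which also changes the effect scale, and that selecting a model partly by efficiency of the arm coefficient is a wider weakness. That is fair, and correcting the link does not cure it.

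Three stronger readings are tempting and are not supported:

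- *The hypothesis test is invalid.* The null is the same on both scales, and the simple simulation showed almost equal size and power.
- *The trial could not report a ratio of means.* The link inverts to a = k × exp(eta)/(1 − exp(eta)), where eta is the linear predictor, so fitted means and their ratio can be computed. What is lost is a single ratio read from the coefficient and constant across covariates.
- *The effect could be wrong by a factor of about 12.* For a true halving, the absolute coefficient is 0.0241 at k = 0.5 with means 20 and 10, and 0.2877 at k = 2 with means 4 and 2. That ratio of 11.9 changes an assumed k and assumed means together, across hypothetical trials. Changing only k (0.5 to 2, means 20 and 10) gives 0.0870/0.0241 = 3.6; changing only the means (k = 2) gives 0.2877/0.0870 = 3.3. Neither is bias within one fitted trial.

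**Conclusion.** The point holds, conditional on the negative binomial candidate being selected for H2, H3 or H4 and fitted as written. The arm coefficient would then not be a log rate ratio. How far it departs rests on assumed values of k and a0, so the tabulated figures are illustrations, not estimates for this trial. The bound on the linear predictor and the mismatch of scales in the selection rule do not depend on those values: the first holds for any positive a and k, the second for any finite k. The bound is incompatible with random effects of unbounded distribution, such as the usual normal; the protocol does not state the distribution.

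The harm is to effect size, interpretation, model choice and fitting. Type I error of the simple two-arm comparison and the planned sample size are not affected. The table should be corrected, but this does not threaten the validity of the trial.

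**What to change.** In Table 1, for H2, H3 and H4, replace the negative binomial entry with log(a). State that the variance is a + a²/k and define k as the dispersion (size) parameter estimated from the data. Both candidates then estimate the same rate ratio and differ only in the variance, so fit and efficiency are compared on one scale. Name the rate ratio as the effect measure for these outcomes.

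The imputation paragraph plans "negative binomial regression to impute count data" without a link; stating the log link there too would keep imputation and analysis consistent.

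The cost is a wording change. The log link is the usual software setting, so there is no extra programming, and the 113 to 120 couples per arm stay as they are.
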